### Sample size, randomisation, and statistics

According to data literature [38, 52] it was estimated that 50 subjects were required to demonstrate an IP reduction of 30% with 80% power and 0.05 significance and considering a 15% drop-out rate. Subjects were randomly divided by using a computer random number generator. The randomisation and allocation were performed by a person not involved in the trial and blinded to the participants, investigators/health care providers and researchers involved in samples analysis. Statistical analyses were performed by means of R statistic software version 3.4.2. Particularly, the following statistical elaborations will be performed to identify significant differences between treatments: (i) the analysis of variance (ANOVA) with repeated measures, (ii) Wilcoxon paired data test, (iii) Linear Mixed Model (LMM) analysis. In addition, regression and correlation analyses (Spearman and Kendal test) are carried out to highlight associations between blood microbiomic data, fecal bacterial profiling data, and physiological and biochemical data. When appropriate, a post-hoc *p*-value adjustment is performed using the Hochberg-Benjamin correction. Significance is set at *P* ≤ 0.05; significance in the range 0.05 < *P* < 0.10 is accepted as trend. Potential gender differences will be also considered in all the analyses.

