### Inclusion criteria

Age ≥ 60 yearsAdequate nutritional status evaluated with Mini Nutritional Assessment (MNA), score ≥ 24Good cognitive status tested with Mini Mental State Examination (MMSE), score ≥ 24Self-sufficiency assessed with validated tests (e.g. Barthel index – activities of daily living, score ≥ 60)Increased intestinal permeability evaluated by serum zonulin level

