### Assessment of food intake

Food intake before (enrollment phase) and during the intervention periods was recorded through the evaluation of OIC Foundation daily menus and the use of WFRs. The daily menus, covering different seasons, were analyzed to quantify nutrient and polyphenol content. Moreover, the day before each time-point, a WFR was completed and both nutrient and polyphenol intake were estimated. At least 3-WFRs were completed during each intervention period. Daily menus and WFRs were assessed using MetaDieta® (Me.Te.Da S.r.l., San Benedetto del Tronto, Italy) to estimate energy and nutrient intake. Total polyphenol estimation was performed by using the Phenol Explorer database (phenol-explorer.eu) to provide estimates of polyphenol concentrations in each food, and where there were no useful values, using our proprietary data or values obtained from the literature. Total polyphenol content of the foods was estimated directly using the Folin-Ciocalteau method [30].

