### Intestinal permeability evaluation

Intestinal permeability was evaluated by quantifying serum zonulin concentrations. Human zonulin is a protein (i.e. prehaptoglobin-2) released by enterocytes able to promote the activation of the signaling transduction pathway that cause tight junction protein disassembly enabling potential bacterial factor translocation [36]. In this study, zonulin serum levels were quantified using the Immunodiagnostik® ELISA kit (Bensheim, Germany) with samples collected in the selection phase and at the beginning and the end of each intervention period. Subjects selection based on IP was performed by considering reference values reported in the manufacturer’s instructions and data published on different target groups [37–39]. Other IP related markers, such as serum CD14 and fecal calprotectin, were also quantified to support the primary outcome.

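### The paired Wilcoxon test, one of three unranked analyses of the diet difference, ignores period; one period-adjusted analysis should be named as primary for zonulin

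*Protocol article*

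**What the plan says.** The Protocol article, under Sample size, randomisation, and statistics, lists repeated-measures ANOVA, the "Wilcoxon paired data test" and a linear mixed model for finding differences between treatments. It ranks none of them and gives no model terms or response definition. On allocation it says "Subjects were randomly divided by using a computer random number generator"; neither the sequence ratio nor any blocking is described.

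Three other places bear on the point:

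- **Design** (MaPLE RCT: protocol and study design): two 8-week diet periods separated by an 8-week wash-out.
- **Entry** (Inclusion criteria): "Increased intestinal permeability evaluated by serum zonulin level". Zonulin is also the primary outcome (Outcome measurements).
- **Measurement** (Intestinal permeability evaluation): zonulin is assayed in "samples collected in the selection phase and at the beginning and the end of each intervention period", so a baseline exists for each period (T0 and T2) separately from the selection sample.

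On background diet, Assessment of food intake states: "The daily menus, covering different seasons, were analyzed to quantify nutrient and polyphenol content".

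**The concern.** In a two-period crossover, anything that moves all participants between the first and second period is a period effect. Two features here make one plausible. People chosen for a high zonulin value will tend to drift down afterwards, and 8 + 8 + 8 = 24 weeks is long enough for seasonal menus to change.

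A signed-rank test on the polyphenol-rich minus control differences cannot separate that shift from noise. Those who took the polyphenol-rich diet first carry the shift with one sign, and those who took it second carry it with the other. This widens the differences and costs power. If the two sequences differ in size, the shift does not cancel and enters the treatment estimate.

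An analysis plan can add period to a mixed model or an ANOVA. It cannot add period to a paired signed-rank test without turning it into a different test. Because no method is named as primary, the one that ignores period could be the one reported for zonulin.

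**Working it through.** **Inputs from the article.** N = 50; "an IP reduction of 30" per cent; "with 80% power and 0.05 significance"; 15% drop-out.

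**Assumptions, because the article gives no figure.** Two-sided test; 1:1 randomised order; SD of the paired difference (SD_d); period shift π; correlations between time points.

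**1. The plan's own figure.** For a paired comparison, n = (SD_d × (1.960 + 0.842) / 0.30)². With 42 evaluable, 42 / 0.85 = 49.4, rounded up to 50, so the stated N fits 42 evaluable participants. No SD is given, so it can only be back-solved: SD_d = 0.30 × √42 / 2.802 = 1.944 / 2.802 = 0.694, or 69% of the mean.

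**2. Equal sequences, period ignored (analytic).** The variance of the paired difference rises from SD_d² to s² = SD_d² + π². Power is approximately Φ(1.944 / s − 1.960).

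| π (% of mean) | s | Power |
|---|---|---|
| 0 | 0.694 | 80.0% |
| 10 | 0.701 | 79.2% |
| 20 | 0.722 | 76.8% |
| 30 | 0.756 | 73.0% |
| 50 | 0.855 | 62.3% |

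This formula treats the shift as random noise. With exactly equal sequences the mean difference keeps its true standard error and only the estimated one is inflated. Power is then Φ((1.944 − 1.960 s) / 0.694), which is 77.7% at π = 20% and 74.7% at 30%. Type I error is 2 × (1 − Φ(1.960 s / 0.694)), which is 4.1% and 3.3%. The loss is therefore about 2-3 points at a 20% shift and 5-7 points at 30%, and the test becomes conservative.

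**3. Equal sequences (simulation; n = 42, 2,000 runs per setting, Monte Carlo error about 1 point).** Wilcoxon on end-of-diet values has power of 75-77% with no shift, 73-75% at a 20% shift and 69-70% at 30%. The period-adjusted model stays at 76-80% throughout. At a 30% shift the Wilcoxon type I error is about 3%, and the mean paired difference is unbiased at −0.30.

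**4. Unequal sequences.** The bias is π × (n₁ − n₂) / n. At a 30% shift:

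- 26:16 gives 0.30 × 10 / 42 = 0.071, about 7 percentage points of the mean.
- 23:19 gives 0.30 × 4 / 42 = 0.029, about 3 points.

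At 26:16 and a 30% shift, the simulated Wilcoxon type I error is about 6-7%, while the period-adjusted model holds 5%. With smaller assumed SDs (log-SD 0.5, within-person correlation 0.5-0.7) it is 7-8% at an 18% shift and 9-10% at a 26% shift. Under unrestricted 1:1 randomisation, the chance of a split at least as uneven as 30:20 among 50 is 0.20. For 26:16 among 42 it is 0.16.

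**5. Adding the baseline difference T0 − T2 to the period-adjusted model.** No shift; all other correlations 0.5.

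| Within-period correlation | Power without | Power with |
|---|---|---|
| 0.5 | 76% | 75% |
| 0.6 | 78% | 79% |
| 0.7 | 78% | 83% |
| 0.8 | 78% | 92% |

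The gain runs from nothing to about 14 points.

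**The case against.** The strongest reply is that a linear mixed model is already on the list, and model terms are what a condensed article leaves to the full protocol or analysis plan. That stands. A reader might infer that no listed analysis uses period or the baselines, or that the ANOVA is a change-score analysis. The article neither states nor excludes those terms, so neither inference is supported. The reply does not cover the paired Wilcoxon, whose lack of a period term is a property of the test.

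A second reply is that regression to the mean and season act on both diets alike, so randomised order balances them. This also stands for near-equal sequences. A reader might infer that drift invalidates the comparison; bias needs unequal sequences. The article does not say randomisation was unrestricted, and a random number generator is compatible with blocking.

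A third reply concerns size. A reader might infer that most of the 80% power is at risk. With log-SD 0.5, within-person correlation 0.5-0.7 and an effect set to give 80% power at n = 42, Wilcoxon power can fall as low as 52% at period shifts of 18-26%. But that effect is only a 16-20% reduction. With the same SDs, the planned 30% reduction leaves the Wilcoxon at 98% or more. The article also reports no zonulin shift between periods, and its Discussion describes a controlled setting with a consistent diet. The period effect is plausible, but its size is unknown.

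**Conclusion.** The point holds in a limited form. The article commits to a between-diet test that cannot account for period, and leaves open whether that test is the primary one for zonulin. With near-equal sequences the estimate stays valid and the loss is modest: about 2-7 points of power for a shift of 20-30% of the mean. With a split such as 26:16 there is also bias, about 7 percentage points of the mean at a 30% shift, with type I error of about 6-7% (up to about 10% under smaller SDs).

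These sizes rest on a back-solved SD_d of 69%, a two-sided test and an assumed period shift, none of which the article states. The case for the baseline covariate is weaker than the case for the period term, because its benefit depends on correlations that are not given.

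**What to change.** Name one primary analysis for zonulin: a linear mixed model on end-of-diet values with diet, period and sequence as fixed effects and participant as random effect. Use T0 and T2 zonulin as the period-baseline covariate, entered as participant mean plus within-participant deviation. Do not use the selection-phase sample as baseline, since participants were chosen on it.

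If a rank test is kept, compare the between-period differences between the two sequences by rank-sum, which removes the period effect. Otherwise label the paired Wilcoxon as a sensitivity analysis only. Report the sequence sizes.

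The cost is two to three degrees of freedom out of about 42 participants and a few lines of text; the zonulin samples needed are part of the existing schedule. Trial status says the trial is complete and analyses are ongoing, so the date of the choice should be recorded, together with whether the diet comparison had already been seen.

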## Methods/design

### MaPLE RCT: protocol and study design

The MaPLE RCT is a single-blind, randomised, controlled, cross-over trial [polyphenol-rich diet (PR-diet) versus control diet (C-diet)] in older people (≥ 60 y) living in a nursing home. Each intervention period consists of 8 weeks and is separated by an 8-week wash-out period in which participants consume their habitual diet to avoid carry-over effects.

The PR-diet and C-diet were developed to provide adequate and comparable levels of energy and nutrients. The PR-diet was achieved by replacing three portions per day of low polyphenol foods/beverages with specific polyphenol-rich foods/beverages (as detailed below). During the study, subjects are asked to fast overnight before each scheduled time-point of blood, urine and feces collection. In addition, daily menus and weighted food records (WFRs) are collected throughout the trial. An overview of the study design is represented in Fig. 1 and Table 1. The study adhered to SPIRIT guidelines.

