### Outcome measurements

The primary selected outcome of the study was zonulin as an IP marker, whereas other IP related markers (e.g. CD14, calprotectin), inflammatory markers (CRP, TNF-α, IL-6), oxidative stress and vascular function markers (DNA damage, VCAM-1, ICAM-1), metabolomics and microbiomics (16S rRNA gene quantification and taxonomic profiling) were included as secondary outcomes to support and validate our study hypothesis.

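### Results with P between 0.05 and 0.10 are called significance and accepted in advance as a trend for every outcome, although the trial is designed and declared at 0.05

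*Protocol article*

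**What the plan says.** All the decision rules stand in one section of the protocol article, Sample size, randomisation, and statistics. The design statement is that "50 subjects were required to demonstrate an IP reduction of 30% with 80% power and 0.05 significance", with an allowance for 15% drop-out. The threshold follows: "Significance is set at *P* ≤ 0.05". After a semicolon, the same sentence adds that "significance in the range 0.05 < *P* < 0.10 is accepted as trend". The added clause names no outcome and so applies to all of them. A Benjamini-Hochberg correction is to be used where appropriate.

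The section Outcome measurements names serum zonulin as the primary outcome. It lists the other permeability, inflammatory, vascular and oxidative-stress markers, with the omics data, and says that these "were included as secondary outcomes to support and validate our study hypothesis".

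**The concern.** The two halves of the sentence do not fit together. The first half makes 0.05 the boundary of significance. The second uses the word significance for a band above that boundary and accepts the band beforehand under a favourable name. No sentence says that such a result is non-significant or that no conclusion follows from it. This is a rule the article states, so it is not a detail left to a fuller document.

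At stake is what the trial may conclude. Someone following the text literally could report zonulin at P = 0.08 as a trend towards lower permeability, or report one secondary marker in the band as backing for the hypothesis. Neither result falls within the error rate for which the trial was sized.

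**Working it through.** **Inputs from the article.** Significance level 0.05; trend band 0.05 to 0.10; 80% power; 30% reduction; N = 50; 15% drop-out. Sidedness is not stated, and two-sided tests are assumed here. No standard deviation is given.

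**The plan's own figure.** 42 evaluable subjects / 0.85 = 49.4, rounded up to 50, so the drop-out step is coherent. The 42 cannot be reproduced without a standard deviation. It can only be solved backwards from the paired formula n = ((z₀.₉₇₅ + z₀.₈₀) × SD / δ)². The implied standardised effect is (1.960 + 0.842) / √42 = 0.432. With δ = 30% of baseline, the SD of the within-subject difference is 30 / 0.432 = 69% of baseline (68% by the noncentral t). This gap does not affect the question about the threshold.

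**Which threshold the 80% belongs to.** At the same effect, power at a two-sided 0.10 cut-off is Φ(2.802 − 1.645) = Φ(1.157) = 0.876 (0.880 by the noncentral t). The stated 80% therefore belongs to 0.05, and the trend band lies outside the design basis.

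**One test under the null.** A simulated paired t-test (n = 42, 200,000 runs) agrees with theory:

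| Label | Either direction | Simulated | Favouring the diet (half) |
|---|---|---|---|
| P ≤ 0.05 | 0.05 | 0.0501 | 0.025 |
| Trend band | 0.05 | 0.0497 | 0.025 |
| Significant or trend | 0.10 | 0.0998 | 0.05 |

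**Count of secondary markers.** CD14, calprotectin, CRP, TNF-α, IL-6, VCAM-1 and ICAM-1 make seven. The section on the comet assay describes two DNA-damage measures, which makes nine. Blood 16S load makes ten.

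**At least one label among k null markers**, assumed independent and unadjusted, is 1 − (1 − p)ᵏ:

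| What is counted | p | k = 9 | k = 10 |
|---|---|---|---|
| Favourable, P ≤ 0.05 | 0.025 | 1 − 0.975⁹ = 20.4% | 1 − 0.975¹⁰ = 22.4% |
| Favourable, significant or trend | 0.05 | 1 − 0.95⁹ = 37.0% | 1 − 0.95¹⁰ = 40.1% |
| Either direction, P ≤ 0.05 | 0.05 | 37.0% | 40.1% |
| Either direction, significant or trend | 0.10 | 1 − 0.90⁹ = 61.3% | 1 − 0.90¹⁰ = 65.1% |

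The favourable rows matter here, because only a change in the hypothesised direction can support the hypothesis. Counting DNA damage once and leaving out blood 16S load gives eight markers, and the favourable figures become 1 − 0.975⁸ = 18.3% and 1 − 0.95⁸ = 33.7%.

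**The case against.** The strongest reply is that the article has only one significance level. Significance and sample size both rest on 0.05, and a separate name for the next band arguably keeps those results apart from significant ones. A reader might infer that the clause sets a second threshold for success and so doubles the stated error rate. The text does not support that: nowhere does it say that a trend meets the primary objective, rejects the null hypothesis or confirms anything. The phrase about supporting and validating the hypothesis explains why the secondary markers are measured and is not tied to the trend band. A per-test rate of 0.10 arises only if trends are read as positive.

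A reader might also infer that a trial with no diet effect would usually produce something supportive, pointing to the 61–65%. That figure counts changes in both directions. It would apply to supportive results only if the tests were one-sided, which the article does not say. Even the 37–40% rests on independence and no adjustment. CRP, IL-6 and TNF-α are related, as are VCAM-1 and ICAM-1, and a Benjamini-Hochberg correction is named. Much of the figure is also ordinary multiplicity, already 20–22% without any trend rule.

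Finally, defining the family for the correction and a formal testing hierarchy commonly belongs in an analysis plan, so their absence here is no finding.

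All of this limits the size of the point. It does not answer the clause itself, which applies the word significance to results the same sentence has just excluded, puts no limit on the outcomes covered, and leaves the meaning of a trend open.

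**Conclusion.** The point holds as a badly fixed rule for interpretation and reporting. The formal alpha is 0.05 and stays there; the sample size, the primary outcome and the effect estimates are untouched. If a trend is taken as a positive finding, which the wording permits without requiring it, the two-sided false-positive rate for zonulin or any other single outcome is 0.10 instead of 0.05 (0.05 instead of 0.025 in the favourable direction). For nine to ten secondary markers, the chance of at least one favourable label becomes about 37–40% instead of 20–22%, a factor of about 1.8. Those percentages assume two-sided tests, independent markers, no true effect and no adjustment. Positive correlation or the correction would bring them down. The change is worth making because it alters what the trial may claim and costs almost nothing.

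**What to change.** Delete the trend clause. State in its place that P > 0.05 is non-significant for zonulin and for every other outcome. Report each outcome as an estimate with a 95% confidence interval and exact P, so that a borderline result is shown with its uncertainty and without a label. Add one sentence saying that secondary markers cannot substitute for a non-significant zonulin result.

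This takes about two sentences and changes neither the sample size nor the data collected. The Trial status section says that analyses were still in progress, so the rule could still be applied to the results. The downside is that some borderline findings lose a favourable label.

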## Discussion

There is growing evidence of a link between IP impairment and increased inflammation [2]. Since aging is characterized by low grade systemic inflammation it is possible that an increase in IP may induce the activation of inflammatory pathways and the immune system caused by the translocation of intestinal microbes, toxins, and/or nutritional components from the gut lumen through the epithelium and into the bloodstream [52]. While there is preliminary mechanistic evidence obtained in animal models on the complex interaction between age-associate microbial dysbiosis, IP and inflammation [5], the properties of the human intestinal barrier, in the context of the ageing process, has not been fully investigated [4]. The dietary pattern and the intestinal microbial ecosystem homeostasis have been addressed as potential key points for the development of strategies to enable healthy aging. The manipulation and/or improvement of the diet by increasing the consumption of food bioactives (e.g. polyphenols) or specific nutrients is recognized as a potential powerful tool to be explored also in the context of IP. However, human intervention studies are still very scarce, and most of these performed using probiotics, prebiotic fibers and dietary supplements [21].

By considering this premise, the MaPLE RCT here described aimed to investigate whether a PR rich-diet can improve the intestinal microbial ecosystem of older subjects characterised by an increased IP. In addition, it is hypothesized that such modulation could promote an overall beneficial impact on IB function, a decreased IP and translocation of inflammogenic bacterial factors in the blood.

The development and management of well-controlled and adequately balanced dietary intervention studies is not an easy task and it becomes even more difficult when the target population is older subjects. Consequently, the first task of the project was dedicated to the optimization of the trial in order to overcome the possible problems related to compliance with the dietary instructions and to other relevant potential confounding factors (e.g. periods of illness or the use of drugs that may be relevant in this target group). For this reason, the MaPLE RCT was planned in a residential area for older people, since it provided a favourable and controlled environment in which it was possible to optimize and standardize most of the important experimental conditions. For example, since outcome data from dietary intervention studies are prone to being affected by individual differences in diets and lifestyle behaviour over time (e.g. during the two eight week periods of dietary intervention), we were able to ensure both strict compliance with the dietary intervention and a consistent dietary pattern among participants by including the polyphenol-rich products in their usual meals provided by the residential home. In addition, the selection of polyphenol-rich foods was based on three important considerations: (i) That the types of foods selected were largely universally liked, (ii) that the texture of the selected products was suitable for older subjects (e.g. with dentition challenges), and (iii) that the portion of food would reliably provide a high dose of polyphenols. In addition, weighed food intake was also assessed to provide us with data to allow accurate estimates of actual nutrient and polyphenol intake in the two periods of treatment (PR- and C- diet). This allowed a high degree of control and substantially reduced between treatments differences.

As regard the primary outcome, serum zonulin concentrations were used as the marker of IP because of the low reliability and applicability of the multi-sugar test in the older population (i.e. due to a high rate of incontinence amongst the elderly participants and the need for adherence to a strict dietary protocol before the test) [52].

It is also noteworthy that the MaPLE RCT is testing, for the first time, the hypothesis that a dietary intervention may modulate quantitatively the bacterial DNA in bloodstream and qualitatively the blood microbiota composition. This should provide further evidence of the impact of the dietary intervention on IP being potentially associated with a reduction in translocation of bacterial factors. Other objectives of the MaPLE RCT are to integrate microbiota profiling data with inflammation and metabolomics data to improve understanding on the impact of the dietary intervention. In addition, the inter-individual response to the treatment will be investigated and food metabolite profiling data will be exploited for the identification of a set of potential biomarkers with relevance in the context of preventing or treating impaired IP.

Finally, results will be pivotal for the development of new dietary approaches and guidelines for managing IP related conditions in the complex context of healthy aging.

